## At the end of the trial, AEs occurring during the study will be summarized in frequency tables (including both the number of each type of AE and the number of distinct participants with each type of AE), by body system and by randomization group.

## 9.3 Interim Analysis Plan Summary

Two interim analyses for the use of the DMC are planned to evaluate the safety and effectiveness of SAVVY relative to the placebo in terms of preventing HIV infection. The first interim analysis will take place after approximately one quarter of anticipated HIV infections (i.e., 16 infections) have occurred and will focus exclusively on safety (with HIV as the primary safety endpoint), and the second interim analysis will take place after approximately one half of anticipated HIV infections (i.e., 33 infections) have occurred and will evaluate both the safety and effectiveness of SAVVY. All analyses will be conducted on a masked basis as follows. Project biostatisticians will prepare and verify the interim analysis programs using randomly generated dummy treatment assignments that have no relationship to the true treatment assignments. An independent biostatistician not otherwise involved with the study will subsequently incorporate the masked treatment codes (i.e. “Drug A” or “Drug B”) into the analysis programs for reporting of interim results. At the request of the DMC, the unmasked treatment codes will be provided separately by an FHI statistician (the Randomization Manager) who is not otherwise involved in the study. The interim analyses will include descriptive statistics (e.g., frequency distributions for categorical variables and means, standard deviations, and ranges for continuous variables) of baseline variables, compliance with intervention, discontinuation rates, intervention-associated morbidity (e.g., epithelial disruptions), and HIV incidence. It is recognized that scheduling restrictions of the study monitors and the DMC may preclude performing the interim analyses at precisely the study quarter- and halfway points, and methods will be employed that accommodate these restrictions.

### 9.3.1 Study size assessment

Prior to the second interim analysis (i.e., after approximately 33 events) of the HIV outcome and prior to examining event rates by masked randomization group, the lead statistician will make recommendations (based on data pooled across randomization groups) regarding adjustment of study size in accordance with the requirement of observing approximately 66 new HIV infections by the conclusion of the study. If either the pooled HIV infection rate or the follow-up rate is substantially lower than anticipated when the study was designed (0.0375 and 0.80, respectively), then consideration will be given to increasing the total study size. Under no circumstances will the statistician recommend decreasing the overall study size. The observed treatment effect at the time of the interim analysis will not be considered as part of this evaluation. Hence no type I error rate adjustment is required to account for this study size assessment.

### 9.3.2 Interim analysis of effectiveness outcomes

Considerations for early termination of the study will be made primarily based on comparisons of the HIV event rates between treatment groups. At the first interim analysis after approximately 16 events, we will ask that the DMC only consider stopping the study for evidence of a potentially harmful SAVVY effect (i.e., evidence that SAVVY enhances HIV transmission), as determined by a one-sided log-rank test at the 0.10 significance level. At the second interim analysis after approximately 33 events, we will ask that the DMC allow consideration for stopping the study either due to evidence of a potentially harmful SAVVY effect, as determined by a one-sided log-rank test at the 0.10 significance level, or due to evidence that SAVVY effectively prevents HIV transmission. The Lan-Demets [16] spending function with O’Brien-Fleming type boundaries [17] will be employed to preserve the overall one-sided type I error rate for effectiveness at the 0.025 level, regardless of the timing of the interim analysis (the effective significance level for the interim analysis will be approximately 0.0026 if the interim analysis takes place at approximately the half-way point). Note that the two one-sided tests at the second interim analysis can also be thought of as a single two-sided test with asymmetric tail probabilities. Furthermore, the liberal significance level used to test for potential harm serves a dual purpose in that it also provides the DMC with a conservative guideline to allow consideration for terminating the study due to futility.

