# 9.0 STATISTICAL SUMMARY

## 9.1 Study Size Justification

A two-sided log-rank test with an overall sample size of 2,142 participants (of which 1,071 are in the SAVVY group and 1,071 are in the placebo group) achieves at least 80% power at a 0.05 significance level to detect a 50% reduction in the HIV infection rate if the rate of infection in the control group is 5/100 person-years and loss to follow-up is at most 20% in both groups. These calculations were conducted using the PASS 2000 software, which assumes exponential models for the times to HIV detection and losses to follow-up. Approximately 66 total HIV infections are required to achieve the desired power.

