It is important to recognize that the proposed test for a potentially harmful effect will not be likely to offer conclusive evidence that SAVVY is indeed harmful relative to placebo. For example, if SAVVY truly has no effect beyond that of the placebo, then the proposed test at the 0.10 significance level has a 10% probability of concluding "potential harm" at the first look and a 15% chance of concluding “potential harm” at either the first or second look. Thus, before recommending that either study should be terminated early due to interim evidence of a potentially harmful effect, the DMC will likely want to consider the emerging evidence from the other study as well. So, for example, if the interim analysis in the Nigeria study after 16 events resulted in a marginally significant p-value of 0.09 but the interim results from the Ghana study indicated that SAVVY may well be protective, then it may be unwise for the DMC to recommend stopping either study. In addition, the DMC will likely consider other evidence from within each of the studies (such as the distribution of AEs across the treatment arms) before making their recommendation.

In order to maintain the overall one-sided significance level for declaring SAVVY effective at 0.025, we will adjust the effectiveness significance level at the interim and final looks using the Lan-DeMets spending function with O'Brien-Fleming type boundaries, as specified in the protocol. If the interim analysis occurs at precisely the halfway point in terms of number of HIV infections, the one-sided significance levels to test for effectiveness will be 0.0026 and 0.024 at the interim and final analyses, respectively.

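### The interim effectiveness level printed for the half-way look (0.0026) is the classical two-look O'Brien-Fleming level; the Lan-DeMets spending function the protocol names gives about 0.0015

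*Protocol*

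**What the plan says.** Section 9.3.2 of the protocol sets the rule for stopping for benefit: "The Lan-Demets [16] spending function with O’Brien-Fleming type boundaries [17] will be employed". The stated aim, whenever the look falls: "preserve the overall one-sided type I error rate for effectiveness at the 0.025 level". The same sentence gives, in parentheses, the level to expect: "the effective significance level for the interim analysis will be approximately 0.0026 if the interim analysis takes place at approximately the half-way point".

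Item 1 of the Protocol Addendum (Statistical Monitoring Plan and DMC Review) names the same function and the same overall level. It fixes the timing more tightly ("If the interim analysis occurs at precisely the halfway point in terms of number of HIV infections") and then states that "the one-sided significance levels to test for effectiveness will be 0.0026 and 0.024 at the interim and final analyses, respectively".

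The information time follows from two other sections. Section 9.1 says "Approximately 66 total HIV infections are required to achieve the desired power". Section 9.3 places the second interim analysis "after approximately one half of anticipated HIV infections (i.e., 33 infections) have occurred and will evaluate both the safety and effectiveness of SAVVY". At the first look, after about 16 infections, "we will ask that the DMC only consider stopping the study for evidence of a potentially harmful SAVVY effect", so that look uses none of the effectiveness error.

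**The concern.** Two rules with similar names give different limits at the half-way point. The classical O'Brien-Fleming boundary is set for a fixed number of equally spaced looks. The Lan-DeMets function of O'Brien-Fleming type is a spending function that can be evaluated at any information fraction, and at one half it is clearly stricter. The protocol names the second and prints the interim number of the first.

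This is the only threshold for considering early termination for benefit. A one-sided p-value between 0.0015 and 0.0026 at 33 infections would meet the printed level and miss the limit of the named method. If that were noticed only after the unmasked result was known, the choice between the two could look data-driven.

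**Working it through.** **Inputs**
- Overall one-sided level for effectiveness: 0.025 (section 9.3.2 and Addendum item 1).
- Effectiveness look at 33 of 66 infections (sections 9.1 and 9.3), so t = 33/66 = 0.5.
- Effect for planning: 50% reduction, hazard ratio 0.5 (section 9.1).
- Assumed: the usual formula for the named function, since the protocol prints none; proportional hazards; 1:1 allocation; log hazard ratio variance 4/d for d infections.

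**1. Which rule reproduces the printed figures?**

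The classical O'Brien-Fleming rule for two equally spaced looks uses limits C/√0.5 and C. C is chosen so that the total crossing probability, from a bivariate normal with correlation √0.5, is 0.025. The solution is C = 1.9774, which gives
- interim z = 2.797, one-sided p = 0.00258;
- final z = 1.977, one-sided p = 0.0240.

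Both printed figures, 0.0026 and 0.024, are reproduced.

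**2. What does the named function give?**

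α(t) = 2[1 − Φ(z₁₋α/₂/√t)], with α = 0.025 and z₁₋α/₂ = 2.2414:
- α(0.5) = 2[1 − Φ(2.2414/0.7071)] = 2[1 − Φ(3.170)] = 0.001525, so interim z = 2.963;
- solving for the final limit that brings the total to 0.025 gives z = 1.9686, p = 0.024500 (0.0244998 before rounding).

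The interim level is therefore 0.0015, and the printed value is 0.0026/0.001525 = 1.7 times as large. The final level, 0.0244998, rounds to 0.024 at three decimals, so the printed final figure fits the named function as well as the classical rule.

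**3. Could another reading of the named function give 0.0026?**

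| Reading | Interim one-sided level |
| --- | --- |
| Spending function, one-sided 0.025, t = 0.48 | 0.0012 |
| Same, t = 0.50 | 0.0015 |
| Same, t = 0.52 | 0.0019 |
| Same, t = 0.55 | 0.0025 |
| Spending function at 0.05, halved per side, t = 0.5 | 0.0028 (final 0.0239) |
| Spending function at one-sided 0.05, t = 0.5 | 0.0056 |
| One-sided 0.025, harm limit at 16 infections treated as binding, t = 0.5 | 0.0015 |

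None gives 0.0026 at half information. The named function reaches 0.0026 only at t = 0.554, that is 0.554 × 66 ≈ 36.6 infections.

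**4. What the difference means at 33 infections**

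Observed hazard ratio at the limit = exp(−2z/√33):
- 0.0026 (z = 2.794): exp(−2 × 2.794/5.745) = 0.378;
- 0.0015 (z = 2.963): exp(−2 × 2.963/5.745) = 0.356.

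Expected z at a true hazard ratio of 0.5 = ln 2 × √33/2 = 1.991. The chance of crossing at this look is
- 1 − Φ(2.794 − 1.991) = 0.211 under 0.0026;
- 1 − Φ(2.963 − 1.991) = 0.166 under 0.0015.

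**5. Overall properties of each pair**

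| Interim / final level | Overall one-sided error | Power at hazard ratio 0.5, 66 infections |
| --- | --- | --- |
| 0.0026 / 0.024 (printed) | 0.0250 | 80.1% |
| 0.0015 / 0.0245 (named function) | 0.0250 | 80.2% |

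**The case against.** The best defence is that the operative rule is the spending function. In section 9.3.2 the number is a parenthetical illustration, marked as approximate and conditional on timing. Section 9.3 says the methods will accommodate looks that miss the planned points, so the limit would be recalculated at the actual count. The Addendum describes its plan as proposed and subject to approval by the sponsor and the DMC, and the stopping rule is framed as guidance to the DMC. All of this is fair, and it limits the weight of the point. It does not rescue the number. A factor of 1.7 is more than approximation, and the Addendum states the figure without that qualifier for a look at exactly half the infections.

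Three stronger readings are tempting, and the documents do not support them.
- *Both printed levels are wrong.* A reader might infer this because the pair matches the classical rule. The final level under the named function also rounds to 0.024, so only the interim figure is shown to be off.
- *The type I error is inflated.* Taking 0.0026 at the interim and then a final level of 0.0245 would give 0.0255. The protocol plans no such mixture: it prints 0.0026 and 0.024 as a pair, and that pair holds 0.025.
- *The chance of early stopping is nearly halved.* Counting whole infections, an 8:25 split gives z = 2.959 and p = 0.00154, which just misses 0.001525, and the stopping chances become 17.9% and 9.5%. That contrast rests on a near-tie under an approximate variance (d/4) for an unstratified split. The planned test is a log-rank test stratified by site (section 9.2.1). The 21% against 17% comparison is the sounder one.

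**Conclusion.** The point stands, narrowed to one number in two places. The interim effectiveness level of 0.0026 in section 9.3.2 and Addendum item 1 is not the level of the method those sections name, which at 33 of 66 infections is about 0.0015 (z = 2.963). The effect is a somewhat easier limit for early benefit than the named rule allows; neither the overall error rate nor the power is harmed.

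The result rests on the usual form of the O'Brien-Fleming-type spending function and on a look at half the information. The hazard ratio limits and stopping chances rest also on the normal approximation with equal allocation. The documents do not show whether the sponsor intended the method or the number. It still merits correction, because it is a decision threshold for stopping a Phase 3 trial for benefit.

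**What to change.** Correct section 9.3.2 and Addendum item 1 together, before the second interim analysis, after the sponsor confirms which rule was intended.

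- *If the spending function was intended.* This fits the protocol better, since it asks for error control whatever the timing of the look. Print about 0.0015 for the interim and 0.0245 for the final analysis (z = 2.963 and 1.969), and say that both apply at 33 of 66 infections and are recalculated at the actual information fraction.
- *If 0.0026 and 0.024 were intended.* Name the classical two-look O'Brien-Fleming boundary in place of the spending function, and remove the claim that error control holds at any timing.

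The cost is a wording change in two places. Under the first option, early stopping for benefit becomes slightly less likely (about 17% instead of 21% at a hazard ratio of 0.5). The number of infections required does not change.

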# 10.0 MONITORING PLAN SUMMARIES

## 10.1 Clinical Monitoring Plan

Site visits by a Clinical Monitor will be made in accordance with FHI standard operating procedures to monitor study operations, the quality of data collected in the research records, the accuracy of the data entered in the database, and to determine that all process and regulatory requirements are met. The monitoring will include assuring that the study is being conducted and informed consent is being obtained according to the protocol approved by the IRBs. The Monitor will make site visits on an approximate quarterly basis during the conduct of the study. A final closeout visit will be made approximately 6 weeks after the last participant has finished the study. A complete monitoring plan will be developed before study initiation.

Investigators will allow the monitors to inspect study documents (e.g., consent forms, drug distribution forms, data collection forms) and pertinent hospital or clinic records for confirmation of the study data.

## 10.2 Data Monitoring Committee

FHI will assemble an independent DMC made up of at least three members; we plan to include at least one clinician and one statistician. The DMC will meet once before the study begins and twice during the study (see Protocol Addendum, p.36). The details for the operation and responsibilities of the DMC will be provided in the DMC Operational Plan.

# 11.0 DATA MANAGEMENT PLAN SUMMARY

A detailed data management plan will be written prior to study initiation. It will be modified if significant changes are required, in order to document how data were handled in the study. The following is a brief summary of the plan.

Study sites will capture clinical data on 2-ply paper data collection forms (DCFs). The Investigator is responsible for the accuracy of data entered on the DCF. The original will be kept in the participant’s original file folder and the other copy will be used as a working copy for data entry and filed in the participant’s working file folder when entry is complete.

The sites will connect to an FHI secure server via the Internet using Citrix software and log directly into FHI's 21 CFR Part 11-compliant data management system. Citrix software allows a user to connect to a host computer and perform processing on the host computer, thus eliminating local software configuration concerns. Once the site data entry staff have logged onto FHI's secure network, they will use the ENTER module of the Clintrial™ data base management system (vendor software provided by Phase Forward, Inc.) The site data entry staff will double enter data (i.e., entry is performed by two independent system users) directly into the Clintrial™ data base. Subsequent data management processing (e.g., query generation, medical coding, data set creation) will take place in the Part 11-compliant environment at FHI.

If data entered on the DCFs are taken from an external source (e.g., laboratory reports, patient records), the source documents should be maintained in the participant’s medical chart or study file at the site, and should be available for review.

Data queries will be generated at FHI and sent to the Investigator every two weeks. The Investigator should answer queries within one week of receipt. The data relevant to the query will be updated based on the Investigator’s written response. Investigators must keep copies of all queries stapled to the DCFs in the participant’s file.

# 12.0 PROTOCOL VIOLATIONS

Emergency departures from protocol that eliminate an apparent immediate hazard to participants and are deemed crucial for the safety and well being of that participant may be instituted for that participant only – the Investigator will contact FHI as soon as possible. The Investigator will notify the IRB and FHI Project Leader in writing as soon as possible and document on the DCF reasons for deviation and ensuing events. Some examples of protocol violations include:

- Omission or inadequate administration of informed consent
- Inclusion/exclusion errors, including legal age limit
- Treatment errors: no treatment or incorrect treatment, including dose or regimen, or expired product
- Missing or incorrectly timed study procedures and assessments
- Forcing a participant to enter or remain in the study
- Participants who should have been discontinued from the study due to protocol criteria, but were not.

# 13.0 STUDY DOCUMENTS

## 13.1 Study Initiation

The following documents will be in place and monitored by a Clinical Monitor at the study site before any potential participants are contacted.

- Investigator’s Brochure
- FDA Form 1572
- Signed protocol and amendments
- Sample DCFs
- Financial disclosure forms for Investigator and Sub-Investigator
- Information given to participants
  - Consent forms
  - Other written information
  - Advertisements
- Financial records
- Signed agreements between involved parties
- IRB approval
- IRB composition
- Regulatory authority approval
- CV for Investigator, Sub-Investigator, and Site Coordinator
- Laboratory test normal values
- Lab accreditation and lab supervisor’s CV
- Instructions for handling of investigational product and trial related materials
- Shipping records
- Decoding procedures for masked trials
- Site Visit Log

## 13.2 Study Conduct

During the study the following documents will be in place and periodically monitored by a Clinical Monitor at the study site. Revision of documents will be made if relevant.

- Revisions to the Investigator’s Brochure
- Revisions to the FDA form 1572
- Revision to the Financial Disclosure forms
- Revision to the protocol and amendments
- Revisions to the DCFs
- Revisions of information given to participants
  - Consent forms
  - Other written information
  - Advertisements
- IRB approvals
- IRB composition changes
- Regulatory authority approvals
- CV for Investigator, Sub-Investigator, and Site Coordinator
- Updates of laboratory test normal values
- Documentation of investigational product and trial related materials shipment
- Relevant communications other than site visits
- Signed consent forms
- Source documents
- Copies of completed DCFs
- Copies of documentation of DCF corrections
- Notification of Investigator to FHI of SAEs
- Notification of Investigator to local IRB and Regulatory Authorities
- Notification by FHI or Sponsor to Investigator of safety information
- Interim or annual reports to IRB, Regulatory Authorities, and FHI
- Participant screening log
- Participant ID code list
- Participant enrollment log
- Investigational products accountability documents
- Staff signature list
- Site Visit Log
- Progress Reports to FHI

## 13.3 Study Completion

After completion of the study, all of the documents in 13.1 and 13.2 should be in the file together with the following:

- Investigational products accountability documents
- Documentation of products destruction (if destroyed at site)
- Complete participant ID code list
- Final report by Investigator to IRB, Regulatory Authorities, and FHI

## 13.4 Site Record Retention and Access to Documents at the Site

The signed original informed consent documents for each participant, yellow copies of DCFs, and originals of all study documentation (e.g. drug inventory forms, participant clinic records, original laboratory reports, diaries, etc.) will be retained by the Investigator for a minimum of two years after USFDA approval or withdrawal of a New Drug Application (NDA). If no NDA is submitted within five years of the last follow-up visit, the center may request permission in writing from FHI to destroy the records. **No records may be destroyed without written permission from FHI.**

The investigator may be subject to a field audit by FHI, Biosyn, or FDA inspectors to validate the participation of study participants and to verify the data reported on the DCFs. This audit could occur while the study is in progress, several years after the study is completed, or when the data are under review by the FDA as part of the pre-market approval process. All of the participants’ records and other study documentation must be filed and accessible on short notice (3-5 days) during the study and subsequent retention period.

